## Research significance

4

The proposed trial will compare the effect of a home-based physical exercise-training programme in the management of femoral fracture to the usual physiotherapy management programmes with specific outcomes of BMD function and inflammatory markers.

## Methods

5

### Phase one

5.1

The first phase of the study will aim to develop an appropriate home-based exercise intervention programme based on evidence from the literature for improved: BMD, immune and inflammatory markers, BMI, function capacity, and HRQOL.

*Study design and procedure*: A comprehensive literature review will be performed to extract evidence on existing exercise-based intervention programme that has been used in the management of lower limb fractures. The concept of the home-based intervention programme will focus on the following—the joint range of motion, muscle strengthening, weight-bearing, proprioception, and gait training. After the exercise programmes have been developed, the programme will be validated with physiotherapists with a speciality in orthopaedics and neuro-musculoskeletal systems. The home-based programme will include cognitive and behavioral strategies that will consist of a discussion of benefits and barriers to exercise and individualized goal setting and self-monitoring of progress by using the exercise adherence and compliance booklet.

### Phase two

5.2

The second phase of the study will aim to determine the effects of physical exercises on BMD, immune and inflammatory markers and functional capacity in adults living with HIV in Nigeria and South Africa with femoral shaft fracture.

*Trial design:* The proposed study design is a multi-center parallel group assessor-blinded randomized controlled trial with allocation ratio of 1:1.

### Study setting

5.3

*Site 1*: The study will be conducted at Chris Hani Baragwanath Academic Hospital (CHBAH), Johannesburg, South Africa, which is a multidisciplinary teaching hospital for the University of the Witwatersrand, Faculty of Health Sciences. Gauteng, with an estimated population of 14.3 million, is one of the nine provinces of South Africa, with Johannesburg as its biggest city with 4.4 million inhabitants.^[1]^

*Site 2:* This is primarily at the Enugu State University Teaching Hospital, Parklane and the University of Nigeria Teaching Hospital, Enugu State, Nigeria. Enugu State, with an estimated population of 3.8 million, is one of the 36 states of Nigeria. The state has an HIV prevalence of 1.3% (Male: 1.0%; Female: 1.6%).^[31]^ There are 20,297 people living with HIV on treatment in 21 treatment facilities.^[31]^ HIV services are offered in 318 centers.^[31]^ The state benefits from the expanded access to ART instituted in Nigeria in 1999 from a national coverage for 359,181 people in 2010 to 747,382 in 2014.^[32]^ Since then, the prevalence of HIV/AIDS in Enugu has risen from 1.3% in 1992, to 5.2% in 2001, and 6.5% in 2005, but declined remarkably to 1.3% in 2012 suggesting that HIV transmission has not shown a stable pattern of decline over the past decades.^[31,33]^

### Eligibility criteria

5.4

The study population will consist of all persons with femoral fracture and HIV-positive and negative (HIV-positive medically confirmed) aged 18 to 60 years attending the above-named health facilities. For the HIV-positive participants, a documented positive HIV result, as well as a history of being followed-up at the HIV treatment and care center.

Inclusion criteria

Only patients between 18 and 60 years at the last birthday and not more than 60 years at the next birthday.For HIV-negative participants, willingness to accept HIV testing.All patients on ART therapy with femoral shaft fracture will be recruited.All patients with lower limb fractures (femur) will be recruited.All patients must be ambulant.

Exclusion criteria

Severely ill persons based on investigator judgment.Presence of any bone or rheumatic disorder.Fracture of the femoral neck.

*Interventions*: The intervention programme will be a home-based exercise programme targeted at improving bone mineral density, function, gait, QoL, and physical activity. The intervention programme aims to improve the joint range of motion, gait training, muscle strengthening, and balance. The participants in the intervention group will be followed up weekly via phone calls to monitor the intervention and ensure adherence to the programme.

*Control group*: The control group will continue with their usual rehabilitation programme as conducted by the various clinics.

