**Methods and design::**

The study is an assessor-blinded randomized controlled trial. Patients managed with internal and external fixation for femoral shaft fracture at the study sites will be recruited to participate in the study. The participants will be recruited 2 weeks post-discharge at the follow-up clinic with the orthopaedic surgeon. The study population will consist of all persons with femoral fracture and HIV-positive and negative (HIV-positive medically confirmed) aged 18 to 60 years attending the above-named health facilities. For the HIV-positive participants, a documented positive HIV result, as well as a history of being followed-up at the HIV treatment and care center. A developed home based exercise programme will be implemented in the experimental group while the control group continues with the usual rehabilitation programme. The primary outcome measures will be function, gait, bone mineral density, physical activity, and QoL.

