### Blinding

5.9

The assessors and the data analysts will be blinded to the participant's assigned groups.

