#### Pilot study

5.11.1

A pilot randomized controlled trials will be conducted to evaluate the feasibility of the study procedure and prepare for unforeseen logistical circumstances. The recruitment process, randomization, intervention protocol, and assessment using the outcome measures exactly as proposed will be tested. A sample of eight participants per group, which is ∼10% of the estimated sample size will be recruited for the pilot trial. After recruitment, baseline (2-weeks post-surgery) assessment of the variables will be measured, followed by a 6-week (post-surgery). The control group will continue with their usual treatment programme. Participants in the experimental and control groups will be re-assessed at the end of the 4-week intervention programme. If there were no changes to the study procedure, the pilot participants would be included in the main study. If there are amendments to the protocol, the changes will be communicated to the relevant bodies.

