### Main study

5.12

The research will recruit patients with femoral fracture being managed at the orthopaedic department at CHBAH, and the following process will be used as a guide for the recruitment, blinding, and allocation. The main study procedure will follow the recruitment, allocation, blinding and intervention guidelines as presented. The CONSORT diagram below in Figure 1 will be used to report the recruitment and allocation of the participants. The time of recruitment and assessment is the usual routine clinic check-up of the patients in the orthopaedic surgery department (2-weeks, 6-weeks, 12-weeks, and 6-months post-surgery).

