### Reporting serious adverse events

5.14

Reports of health deterioration warranting hospitalization or resulting in the death of any participant will be reported to the PI within 24 h. All participants must be informed of such developments within 72 h and be required to re-consent to continue with the trials.

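### Only the exercise arm gets weekly study calls while safety capture waits for reports, so serious events may be heard of sooner, and possibly more often, in that arm

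*Protocol article*

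**What the plan says.** All places are in the protocol article.

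- **Calls (5.4, Interventions):** "The participants in the intervention group will be followed up weekly via phone calls to monitor the intervention and ensure adherence to the programme". The stated purpose is monitoring and adherence. No adverse-event question is mentioned, and no duration is given for the main study.
- **Control (5.4, Control group):** "The control group will continue with their usual rehabilitation programme as conducted by the various clinics". No study call or other added contact is stated.
- **Safety rule (5.14):** "Reports of health deterioration warranting hospitalization or resulting in the death of any participant will be reported to the PI within 24 h". The rule covers everyone in the trial, but it starts from a report. The same section then requires all participants to be told within 72 h and to re-consent.
- **Shared visits (5.12):** "2-weeks, 6-weeks, 12-weeks, and 6-months post-surgery".
- **Programme length (5.11.1, pilot only):** "Participants in the experimental and control groups will be re-assessed at the end of the 4-week intervention programme".
- **Blinding (5.9):** "The assessors and the data analysts will be blinded to the participant's assigned groups". Participants are not named as blinded.
- **Outcomes:** "The primary outcome measures will be function, gait, bone mineral density, physical activity, and QoL" (abstract). Neither Table 1 nor section 5.15 contains an adverse-event outcome or a test of harm.

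**The concern.** Section 5.14 can act only on what someone reports. By design the study speaks to one arm every week and to the other only at routine visits. A caller who asks whether the exercises are being done may learn that the patient has been admitted, or from a relative that the patient has died. In the control arm the same event may stay unknown until the next visit. If the patient does not attend, it may look like ordinary loss to follow-up.

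Two things are at stake. First, a descriptive table of serious events by arm could show more or earlier events under exercise for no reason other than contact. Equally, a true excess could be explained away as a product of the calls. The introduction itself says that the safety of exercise in HIV has not been fully investigated. Second, reports set off the information and re-consent process in 5.14, so faster detection in one arm affects when that process starts.

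Both features are choices about data collection. No later analysis can recover a control-arm event that nobody heard about.

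**Working it through.** The document states no adverse-event rate, capture rate or harm test, so there is no figure to reproduce. The check compares the two contact schedules.

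**Inputs.** Visits at weeks 2 (baseline), 6, 12 and 6 months (5.12), with 6 months taken as 26 weeks. Weekly calls in the exercise arm only (5.4). Programme length of 4 weeks (5.11.1, pilot). Section 5.7 counts recruitment from discharge, not surgery, so the counts are approximate.

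**Step 1: study contacts after baseline.**
- Control: 3 visits.
- Exercise, calls tied to a 4-week programme: 6 − 2 = 4 calls, plus 3 visits.
- Exercise, calls to 6 months: 26 − 2 = 24 calls, plus 3 visits.

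**Step 2: longest wait until the next study contact.** This assumes an event becomes known only at a study contact. It is a worst case, because patients, relatives or clinics may report earlier.

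| Window | Control | Exercise, calls to week 6 | Exercise, calls to 6 months |
|---|---|---|---|
| Weeks 2–6 | 6 − 2 = 4 weeks | 1 week | 1 week |
| Weeks 6–12 | 12 − 6 = 6 weeks | 6 weeks | 1 week |
| Weeks 12–26 | 26 − 12 = 14 weeks | 14 weeks | 1 week |

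If calls stop at week 6, the arms differ only in the first window, which a shared visit closes. If calls run to 6 months, the arms differ throughout, most in the last window.

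**Step 3: number of events, as illustration only.** With equal true risk in both arms, the apparent risk ratio is the capture rate under exercise divided by the capture rate under control. All capture rates here are assumed:
- 100% against 90%: 1.00/0.90 = 1.11
- 95% against 80%: 0.95/0.80 = 1.19
- 90% against 50%: 0.90/0.50 = 1.80

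The ratios only restate the assumptions. If hospitalisations and deaths are almost fully known in both arms by 6 months, the ratio is near 1 and the difference that remains is in timing.

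**The case against.** The case on the other side is substantial.

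- **The calls are for adherence.** This is correct, and no adverse-event enquiry is described. Still, asking why exercises were missed is a natural route to hearing of an admission or death, so the chance of unequal ascertainment remains.
- **The only stated programme length is 4 weeks.** If the calls follow it, the 14-week gap is the same in both arms. This stands, and it limits the asymmetry to about weeks 2–6 in that case. The main-study duration is not stated, so the longer case is not excluded.
- **The rule covers any participant and only hospitalisation or death,** the events least likely to escape shared visits. Control patients also have clinic rehabilitation, and HIV-positive patients in both arms have a history of HIV-clinic follow-up. This largely stands and is why timing is the main issue. It is not complete cover: no Table 1 instrument records adverse events, and a patient who has died or is in hospital elsewhere may miss the visit.
- **No between-arm harm comparison is planned.** This stands. The point bears on descriptive tabulation and on the timing of action under 5.14.
- **An article condenses the protocol.** Section 5.13 refers to a case record form and operating procedures that are not shown. A common enquiry may exist there. The one-sided calls and the report-based rule, however, are in the text.

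A reader might infer that events will be found more often under exercise, that any harm comparison is biased, or that control patients go unobserved for months while exercise patients do not. The documents support none of these: the content and duration of the calls are not given, other routes to a report exist, and capture rates are unknown.

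**Conclusion.** The point holds as a risk of unequal ascertainment, not as a demonstrated bias. Serious events may reach the investigators sooner, and possibly more often, from the exercise arm while calls continue. The asymmetry is about 4 extra contacts if calls end with a 4-week programme, or about 24 if they run to 6 months. Both figures assume one call a week from the 2-week baseline, and the first assumes that the pilot's programme length carries over.

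For hospitalisation and death the effect is mainly on timing. Its size cannot be derived from the document, and the ratios in the illustration should not be quoted as estimates. The efficacy outcomes are not touched by this point. It is a modest weakness that is cheap to repair.

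**What to change.** Amend section 5.14 as follows:

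1. The blinded assessor asks the same scripted adverse-event question in both arms at the shared 6-week, 12-week and 6-month visits and records the date of onset.
2. Vital status and the reason for any missed visit are established in the same way in both arms.
3. The source of each event is recorded (visit question, weekly call, clinic, other).
4. The by-arm safety tabulation rests on events ascertained by these common routes. Events known only from the weekly calls are shown separately, not dropped.
5. Reporting of all events within 24 h stays as it is, whatever the source.

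Stating in 5.4 how long the calls run in the main study would let readers judge the remaining asymmetry.

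**Cost:** protocol and case record form wording, one question at existing visits, and some tracing of patients who do not attend. No visit is added and treatment does not change. The main downside is that the principal tabulation relies on recall at visits. An answer may also reveal the allocation to the assessor, so the question is best asked after the outcome measurements.

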### Outcomes

5.5

Table 1 outlines the outcome measure, tools, validity, and reliability for the study.

**Table 1 T1:** Psychometric measures.

Outcome measure	Instrument	Reliability and validity
Bone mineral density	Portable Xrite 331C densitometer (quantitative ultrasound densitometer)	The Portable Xrite 331C densitometer is valid instrument to measure bone density. The test-retest reliability of the portable densitometer will be determined in this study.
Laboratory tests	**Bone resorption**: Serum Beta-CTx or Carboxy-terminal telopeptide cross-linked type 1 collagen (CTX) **Bone formation**: osteocalcin **Pro-inflammatory markers**: C-reactive protein (CRP) **HIV clinical markers:** HIV test, CD4 count, viral load and albumin **Other bone metabolism biomarkers**: calcium and magnesium	The test will be performed using the Roche Cobas 8000 analyser. The tests have high repeatability using human samples in accordance to the Clinical and Laboratory Standards Institute (CLSI) EP5 requirements.
Functional capacity	WHODAS^[34]^	WHODAS is a valid and reliable (α = 0.94) tool used in measuring physical and functional health^[34]^
Health-related quality of life	EQ-5D questionnaire^[35]^	EQ-5DL is a valid and reliable tool (ICC = 0.87) in chronic musculoskeletal problems.^[36,37,38]^
Gait speed	4 m gait speed	The 4 m gait speed test is a reliable (ICC = 0.715) and valid test for measuring general health and muscle mass ^[39]^.
Gross muscle strength	Hand held isokinetic dynamometer *r* = 0.40 – 0.71; intertester ICC = 0.82– 0.84	The handheld dynamometer is a valid and reliable tool in assessing gross muscle strength.^[40–42]^ Intertester and intratester reliability—ICC = 0.82 – 0.8 and ICC = 0.91 – 0.94. The HHD shows a significant positive correlation with step length and reaction time (*r* = 0.40 – 0.71; *P* < .05) ^[41]^.
Anthropometric measures (weight, height and BMI)	Stadiometer and weighing scale	The stadiometer and weighing scale will be calibrated before each use.
Body composition	Fat loss monitor with scale (OMRON HBF – 400)	Weight is measured in 0.2 lb increments. Body fat percentage is measured from 5% to 60% in 0.1% increments. BMI is rated from 7.0 to 90.0 in 0.1 increments^[43]^.
Physical activity	Short-form International Physical Activity questionnaire (IPAQ-SF) The Yamax Digiwalker SW200 pedometer will be used to objectively quantify physical activity.	The IPAQ-SF is a seven-item valid and reliable tool in measuring self-reported physical activity in the last seven days^[44,45]^. The Yamax Digiwalker SW200 has been used in several epidemiological studies involving the evaluation of free-living physical activity^[46,47]^. The pedometer is considered a reliable and validated tool for intervention and observational studies of physical activity levels among young people^[48]^.
Adherence	Exercise Adherence Rating Scale^[49]^	The exercise adherence rating scale is a valid and reliable (α = 0.81) tool in measuring exercise adherence^[49,50]^. Test-retest reliability, ICC = 0.97^[49]^.
Coping	COPE Inventory^[30]^	The COPE inventory is a reliable and valid tool in assessing coping strategies with chronic problems^[51]^.

### Participant

5.6

*Sampling and sample size:* Consecutive sampling will be used to recruit the participants. Using the statistical superiority sample size design,^[34]^ a sample of size of 36 participants per group will be sufficient to show a statistical difference in the bone mineral density between the control and the experimental group. For this study, the groups are divided into four which are the experimental group (HIV+ and HIV−) and the control group (HIV+ and HIV−), therefore, at least a total of 144 patients per study site will be recruited to participate in the study. The sample size will be calculated using Equation 1:(1)$$N=2\times \left\{Z_{1-\alpha /2}+Z_{1-\beta }/d2\right\}\times Pooled\;SD$$

where N = total sample size per group, *Z*_1−α/2_ = 1.96, *Z*_1−β_ = 0.845, *d*^2^ = 0.1 and pooled standard deviation = 0.093.

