### Statistical analysis

5.15

Data to be collected shall include discrete and normally distributed continuous variables. The normal distribution of the continuous variables will be tested using the Shapiro–Wilk test, and depending on the outcome, parametric or non-parametric statistics will be used to analyze the data. The change in the categorical outcomes across the time points will be measured using the McNemar's test. The difference in the continuous outcomes between the groups will be measured using the independent *T*-test (parametric) and Mann–Whitney *U* test (non-parametric). Intention to treat analysis method will be used for this study. Alpha shall be set at *P* < .05 (two-tailed). All analyses will be intent-to-treat and missing data will be treated as missing.

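### Protocol article, section 5.6: Equation 1, its inputs and the stated 36 per group are mutually inconsistent; 36 cannot be derived as written

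*Protocol article*

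**What the plan says.** Section 5.6 (Participant) of the protocol article states that "a sample of size of 36 participants per group will be sufficient to show a statistical difference in the bone mineral density" between control and experimental arms. It then counts four groups, the two arms each split by HIV status, and concludes that "at least a total of 144 patients per study site will be recruited to participate in the study".

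Equation 1 is printed as N = 2 × {Z(1−α/2) + Z(1−β)/d2} × pooled SD. The legend begins "where N = total sample size per group". It gives 1.96 and 0.845 for the two Z values and ends with the squared difference and the spread: "0.1 and pooled standard deviation = 0.093". No units are given, and no allowance for loss to follow-up appears.

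Other sections agree with these inputs. Section 5.2 gives an "allocation ratio of 1:1", and section 5.15 sets a two-tailed 5% level. Section 5.3 describes two sites, Johannesburg and Enugu.

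**The concern.** Section 5.6 gives a formula, every input and a result, so the calculation can be checked without any other document. The printed equation lacks the squares that a two-means formula needs: neither the sum of the Z values nor the SD is squared, and only the second Z value is divided by d2. The input labelled as a squared difference is 0.1, where a difference is what a reader would expect.

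This is the only justification given for the trial's size. If it cannot be reproduced, a reader cannot tell which BMD difference the trial was designed to detect, with what power, or in which comparison.

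**Working it through.** **Inputs (section 5.6):** Z(1−α/2) = 1.96; Z(1−β) = 0.845, which corresponds to 80.1% power; 0.1, labelled d²; pooled SD 0.093; N per group. The Z values sum to 2.805, and 2.805² = 7.868.

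**Attempts to reproduce 36 from these inputs**

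| Reading | Calculation | N per group |
|---|---|---|
| As printed | 2 × (1.96 + 0.845/0.1) × 0.093 | 1.94 |
| Z-sum over 0.1, nothing squared | 2 × (2.805/0.1) × 0.093 | 5.2 |
| Z-sum squared, d² = 0.1, SD not squared | 2 × 7.868/0.1 × 0.093 | 14.6 |
| Standard formula, d² = 0.1 | 2 × 7.868 × 0.093²/0.1 | 1.36, so 2 |
| Standard formula, d = 0.1 | 2 × 7.868 × 0.093²/0.1² | 13.6, so 14 |
| d = 0.1, SD not squared | 2 × 7.868 × 0.093/0.1² | 146.3 |

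None gives 36. With the t-distribution, the standard formula at d = 0.1 gives 14.6, so 15.

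**Variants that depart from the stated inputs (d = 0.1, SD 0.093)**
- One-sided test at 80% power: 11.
- Two-sided test at 90% power: 19; at 95% power: 23.
- Alpha 0.0125 at 80% power: 20.
- Inflating 14 for an assumed loss of 10% to 50%: 16 to 28. To reach 36, the loss would have to be 1 − 14/36 = 61%.
- More extreme settings come close (alpha 0.025 with 99% power gives 37), but they abandon both printed Z values.

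**The one near-match from the stated inputs.** 146.3/4 = 36.6, and 4 × 36 = 144. This puts 0.093 where a variance belongs and divides a per-group N by the four groups, contrary to the article's own definition of N.

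**What 36 would imply on the standard formula**
- SD needed at d = 0.1: 0.1/(2.805 × √(2/36)) = 0.151, not 0.093.
- A squared difference of 0.1, taken literally, means d = √0.1 = 0.316, which is 0.316/0.093 = 3.4 SD.

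**What the planned size delivers.** Thirty-six is one arm in one HIV stratum at one site. Pooling strata within a site, or the two sites within a stratum, gives 72 per arm; pooling both gives 144.

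*If 0.093 is an SD:* the difference detectable at 80% power is 2.805 × 0.093 × √(2/n).
- n = 36: 0.061 (0.062 with the t-distribution). Power for 0.1 is 99.5% (99.4% with the t-distribution).
- n = 72: 0.043 to 0.044.
- n = 144: 0.031.

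*If 0.093 is a variance:* power for 0.1 is Φ(0.1/√(2 × 0.093/n) − 1.96).
- n = 36: Φ(1.391 − 1.96) = 28%. About 146 per group would be needed for 80%.
- n = 72: Φ(1.967 − 1.96) = 50%.
- n = 144: Φ(2.782 − 1.96) = 79%.

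**The case against.** The strongest reply is that section 5.6 claims only that 36 is enough. With d = 0.1 and an SD of 0.093, 14 or 15 are enough, so 36 is too and the claim is true. That stands for the SD reading. A reader might infer from the failed derivation that the trial is underpowered. The article does not support this, because it calls 0.093 an SD, and on that reading the size is generous.

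A second reply is that superscripts may have been lost in typesetting or text extraction. That may explain the form of the equation but not the result: with the squares restored, the same inputs give 14 or 2.

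A third is that 0.062 is not the trial's detectable difference. This also stands. The size is set per site and per HIV stratum, and pooled comparisons of control with experimental arms detect smaller differences. Any restated figure must name its level.

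A reader might also conclude that a null BMD result could not be interpreted. That goes too far. The result would be read from the estimate and its confidence interval, which use the observed spread. What is lost is the prospective rationale for the size.

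**Conclusion.** Wrong as written. Equation 1, its inputs and the 36 per group cannot all be right. The inputs support 14 or 15 per group at d = 0.1, or 2 if 0.1 really is the squared difference. The stated 36 is about 2.5 times the first of these (36/14 = 2.6; 36/15 = 2.4).

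The consequence depends on a fact that only the authors can supply:
- If 0.093 is an SD, the error is in the derivation and in the power it implies: about 99% for a difference of 0.1 at 36 per group, not 80%.
- If 0.093 is a variance, as the only near-route to 36 would require, 36 per group has about 28% power for 0.1. Sufficiency then cannot be claimed per group, and even with both sites and both strata pooled the power is about 79%.

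The near-match is a numerical coincidence or a clue; it does not prove how 36 was obtained. All figures assume a two-sided 5% level, 1:1 allocation, complete data and, for the pooled figures, that both sites recruit 144.

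**What to change.** In section 5.6:

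1. Replace Equation 1 by n per group = 2 × (1.96 + 0.845)² × SD² / d².
2. State d itself, not its square, and give d and SD in the units of the BMD measure.
3. Confirm first whether 0.093 is an SD or a variance.
4. Show the arithmetic to N and name the comparison it serves: within stratum and site, pooled over strata or sites, or pooled over both.
5. Restate what the planned size delivers at that level. If 0.093 is an SD, 36 per group gives 80% power for about 0.062 within one stratum at one site; the pooled figures are about 0.043 to 0.044 at 72 per arm and 0.031 at 144. If it is a variance, withdraw the claim for 36 per group or restate it for the fully pooled comparison (about 79% power for 0.1).
6. Label any figure after dropout as an assumption, since the article gives no loss rate.

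Cost: if 0.093 is an SD, this is a rewording of one section and needs no change in recruitment. If it is a variance, the authors must either restate the claim at the pooled level or reconsider the number of patients, so the cost cannot be fixed until point 3 is answered.
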